## Stepwise procedure

The stages of the study procedure are illustrated in Figure 1. The study includes two measurement time points (pre- and post-intervention) which are performed in a laboratory at the ETH Zurich (Hönggerberg, Switzerland). The two data collection sessions are performed by treatment-blinded investigators including the following assessments: TMS measurement, EEG measurement, TAP performance, gait performance, and questionnaires (short FES-I, MMSE, and GDS). The pre-measurement consists of a screening and measurement part. The screening part contains data of the MMSE, GDS, and health questionnaire (including questions about physical impairments, medical history, anthropometric data, and physical activity level) and is used to determine eligibility for the measurement part and study participation, respectively. The measurements for each session take about 2 h and are conducted to determine the effects of the interventions on brain structure and function. The pre-intervention measurement is planned to be performed in the week before the intervention starts. The post-intervention measurement is planned for the first week after the intervention, while the possibility consists to postpone the measurement by one week. In addition, blood samples are taken at pre-intervention measurement, after 16 weeks of NS intervention, and at post-intervention measurement.

**Figure 1 F1:**
[figure not shown]
**Flow chart of study procedure. FA: fatty acid**.

The intervention starts on Monday of the week following the pre-intervention measurement and lasts 26 weeks. Each day for 26 weeks, the participants have to take the same amount of NS regularly at home, while the intake time point should be as consistent as possible. The investigators can reproduce the intake using the individual intake protocol of each participant. After 16 weeks, the participants start with the exergame training lasting for 10 weeks. In small groups, each participant trains three times per week for 30 min. The training time points are individualized for each participant and may also be variable from week to week for individual participants. Each participant has to attend at least 70% of training to be considered for (per protocol) analysis.

## Anticipated results

The results of this study can be influenced by several factors. One might be the adherence to regular intake of the NS. As countermeasures an intake protocol supports the participant and helps the investigator to control the intake. Blood sample analysis is an additional control measure. Moreover, the training attendance is checked by the investigators, so that each participant reaches at least 70% attendance. However, a higher drop-out rate may be expected because of the long trial duration. The aforementioned sample size calculation included the calculated 25 participants and five additional participants for each intervention group because of the expected drop-outs. Moreover, TMS is used in this study as an indirect proxy measure of synaptic plasticity. Based on the results of this study future studies should focus on more direct measures of synaptic plasticity by using either magnetic resonance tomography (Alvarez-Salvado et al., 2014) or positron emissions tomography scans (Magistretti, 2006) for comparing the brain scans before and after the intervention.

The aim of this study is to investigate the neuronal effects of an intervention that combines exergame training with omega-3 FA supplementation. Several animal studies combined omega-3 FA and PE focusing on the neuronal effects and the possible underlying mechanism. One study concluded that omega-3 FA interacts with PE in improving the axonal growth, synaptic plasticity, and cognitive function of the adult rat brain (Chytrova et al., 2010). Omega-3 FA and PE might act both on the energy metabolism of hypothalamus and hippocampus thereby influencing brain plasticity and cognitive function (Gomez-Pinilla and Ying, 2010). Moreover, the combination may increase the level of brain-derived neurotrophic factor resulting in the activation of CREB and synapsin I (Wu et al., 2008). The activated metabolic pathway supports neuroplasticity and cognition. So far, no comparable human study exists that combines PE, especially exergame training, and omega-3 FA. The trial design is based on the results of the aforementioned animal studies and of the sole administration studies of either exergame training or omega-3 FA for older participants focusing on the brain. An exergame intervention was chosen because a combination of cognitive and motor training is expected to have positive effects on the elderly brain (Bamidis et al., 2014; Law et al., 2014; Schättin et al., 2016) and is able to ameliorate EFs in older adults (Eggenberger et al., 2016; Schättin et al., 2016). Motor training builds new synaptic connections while the cognitive part supports the preservation of the new build structure. In aging humans, PE can strengthen neuronal structure, synaptic plasticity, and transmission as well as cognitive function (Cai et al., 2014). PE might trigger molecular and cellular mechanisms supporting brain plasticity (Cotman et al., 2007). Furthermore, video game-based training serves as a powerful tool to train cognitive abilities (Zelinski and Reyes, 2009; Kueider et al., 2012), including attention and EFs (Jobe et al., 2001) as well as to evaluate functioning of underlying neuronal mechanisms explaining cognitive control (Anguera et al., 2013). In normal aging humans, omega-3 FA might improve cognition (Janssen and Kiliaan, 2014) and ameliorate brain deterioration through the positive effects on brain structure, function, and cerebral blood flow (Haast and Kiliaan, 2015). A recent randomized-controlled trial showed that omega-3 FA had positive effects on EF, white matter microstructure integrity, gray matter volume, and vascular parameters (Witte et al., 2014). Both interventions, exergame training and omega-3 FA, are believed to act on the same (metabolic) brain pathways and, therefore, complement each other (Gómez-Pinilla, 2008). The brain gets trained during the exergame training and the omega-3 FA might, in this case, provide the needed substance and energy to build up new structures and to support metabolic pathways. An interaction is created that might be more effective for brain structure and function compared to the sole administration of an individual intervention component.

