A systematic review revealed that previous interventions using a combined approach of PE and NS to effect on the brain were not particularly successful because of the misfit between the combinations; the intervention components were not selected based on sharing of similar neuronal mechanisms (Schättin et al., 2016). The review indicates, however, that especially fish oil, containing omega-3 fatty acid (FA), might be an effective NS supporting the positive effects of PE. Omega-3 FA is important for energy metabolism and for the composition of the plasma membranes in the brain (Gómez-Pinilla, 2008). Another review showed that long chain polyunsaturated FA (LCPUFA) might improve cognition, decrease (neuro) inflammation, and reduce vascular risk factors in normal aging adults (Janssen and Kiliaan, 2014). Omega-3 LCPUFA may provide decreased brain deterioration through the positive effects on brain structure, function, and cerebral blood flow (Haast and Kiliaan, 2015). A recent randomized-controlled study showed that fish oil had positive effects on brain structure and function in healthy older adults (Witte et al., 2014). The participants showed improved EFs, white matter microstructure integrity, gray matter volume, and vascular parameters.

So far no study investigated the combined effect of exergame training and omega-3 FA on the elderly brain's structure and function. This study, therefore, aims to investigate the effects of a combination of exergame training and omega-3 FA. The following research question will guide through the research process: “Does the combination of exergame training and fish oil differently affect neuronal system levels in the elderly brain compared to exergame training alone?” The main objectives of the trial are (1) to determine the effects of the intervention on the neuronal structural level of the brain (neuronal excitability) and (2) to assess the effects on functional level in the brain (neuronal activity). We hypothesize that the combination will differently affect these parameters.

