### Sample size

To avoid a type I or II error, the power calculation was based on a study examining the effect of omega-3 FA on EEG frequency band distribution during a sustained attention test (Fontani et al., 2005). The aforementioned study was used for sample size calculation because so far there exists no study that examined the influence of exergame training in combination with omega-3 FA on neuronal systems using TMS or EEG methodology. Due to the values of EEG frequency band distribution during sustained attention tests (with values K + K = 27.70 ± 5.2; K + K = 31.49 ± 8.6), an estimated sample size of 24 participants would result in 80% power at an alpha-level of 0.05 for this parameter. To account and compensate for expected drop-outs, the study includes 30 participants in each group. Drop-outs are expected because of the long study duration of 26 weeks, the age of the participants, and numbers are based on previous reports on adherence of non-institutionalized older adults to exercise programs (Nyman and Victor, 2012).

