### Statistics

The data analysis will be performed at the end of intervention including the measurement values from pre- and post-intervention measurements. Data will be tested for normal distribution using Shapiro-Wilk test and Q-Q-plots. A 2 × 2-ANOVA will be used with normally distributed data, the non-parametric equivalent for data not fulfilling assumptions of normal distribution. The test will be used to compare the two interventions over time (from pre- to post-measurement) on changes on the main dependent variables MEP, RRP, RT of cognitive tasks, spatio-temporal gait parameters, DTC, and FA levels. In addition to statistical significance testing effect size calculation (*r* = Z/√N) will be performed. The participants' FA blood levels, demographic, and health information will be examined in relation to the outcome measures in order to interpret the results in context. All statistical procedures will be conducted with the IBM Statistical Package for the Social Science software package. A probability level of *p* < 0.05 will be considered to be statistically significant.

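### One sample size calculation is reported as 24 participants in one section and 25 per group in another, and the 24 is not labelled per group or total

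*Protocol article*

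**What the plan says.** Two sections of the protocol article describe the calculation.

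- **Sample size (Materials and methods).** From two printed means and SDs, 27.70 ± 5.2 and 31.49 ± 8.6, the article concludes that "an estimated sample size of 24 participants would result in 80% power at an alpha-level of 0.05 for this parameter". The sentence does not say per group or in total. The section then states: "To account and compensate for expected drop-outs, the study includes 30 participants in each group". It bases the expected losses on cited reports of adherence among older adults, but prints no percentage.
- **Anticipated results.** Referring back to that same calculation, the section says that it "included the calculated 25 participants and five additional participants for each intervention group because of the expected drop-outs".

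The enrolled number is consistent throughout: 60 in the Abstract, 30 per group in the Sample size section, and a randomization list running from 001 to 060 in the section on blinding, randomization and allocation.

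**The concern.** The article contains only one sample size calculation, and the Anticipated results section points back to it explicitly. A single calculation cannot have returned both 24 and 25. Both figures are current text in running prose, so neither an amendment history nor a damaged table explains the difference.

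At stake is how clearly the plan can be read. The calculated number tells readers how many evaluable participants the design was meant to deliver, and its distance from 30 tells them how much loss was allowed for. Since no drop-out rate is printed, that allowance can be recovered only by subtraction, and the two sections give different answers. The missing label on the 24 adds a second ambiguity.

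**Working it through.** **Inputs**

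- Calculated number: 24, unlabelled (Sample size); 25 per group (Anticipated results).
- Enrolled: 30 per group (Sample size).
- Means and SDs: 27.70 (5.2) and 31.49 (8.6) (Sample size).
- Power 80% and alpha 0.05 (Sample size). The Statistics section adds only that "A probability level of *p* < 0.05 will be considered to be statistically significant", without sidedness. The hypothesis is non-directional ("We hypothesize that the combination will differently affect these parameters"), so two-sided is the natural reading.

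**Step 1. Can the calculated figure be reproduced, and does that settle 24 or 25?**

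Difference = 31.49 − 27.70 = 3.79. Pooled SD = √((5.2² + 8.6²)/2) = √50.5 = 7.106. Standardized difference = 3.79/7.106 = 0.533.

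For two independent groups, n per group = 2 × (z_alpha + z_power)² × SD² / difference²:

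- Two-sided: 2 × (1.960 + 0.842)² × 50.5 / 3.79² ≈ 55.2, so 56 per group (57 with the t distribution).
- One-sided: 44 per group (45 with the t distribution).

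Neither 24 nor 25 follows. A figure of 24 appears only under readings that the article does not state:

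- One-sided test using the smaller SD of 5.2 alone: 24 per group (t-based 23.98).
- One-sample, one-sided test with standardized difference 0.533: 23.15, so 24 in total.
- Two-sided paired test: 28 pairs at an assumed correlation of 0.6 and 23 at 0.7, so about 24 with a correlation near 0.7.

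Some of these give a number per group and others a total, so the arithmetic does not settle the missing label.

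**Step 2. Implied drop-out allowance with 30 enrolled per group**

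Allowance = 1 − evaluable/enrolled.

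- Target 24 per group: 1 − 24/30 = 20.0%, or 6 spare.
- Target 25 per group: 1 − 25/30 = 16.7%, or 5 spare.

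The 20.0% depends on reading 24 as per group.

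**Step 3. How much does one participant per group matter?**

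Power from the noncentral t distribution, with noncentrality 3.79 / (SD × √(2/n)):

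| Assumption | 24 per group | 25 per group | Change |
|---|---|---|---|
| Two-sided, SD 7.106 | 44.0% | 45.5% | 1.5 points |
| Two-sided, SD 5.2 | 69.6% | 71.4% | 1.8 points |
| One-sided, SD 5.2 | 80.0% | 81.5% | 1.5 points |

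In the standard reading (first row), all 30 per group evaluable would give 52.8%.

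**The case against.** The strongest reply is that this is a one-unit slip with no operational effect. Each section is coherent in itself (24 + 6 = 30 and 25 + 5 = 30), every statement of enrolment agrees, and nothing in the article makes a stopping rule, analysis set or success criterion depend on 24 or 25. The differing allowances are not a second error, because they follow automatically from the first. All of this stands and limits the size of the point. It does not remove the contradiction, since both sections print a result for the same calculation and the results differ.

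A reader might also infer more than the documents support:

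- **That the article states conflicting drop-out rates.** It states none; 20.0% and 16.7% are subtractions from 30.
- **That enrolment is too small for the target.** Dividing 25 by 0.8 gives 31.25, hence 32 per group, 4 more in total than the 60 planned. This pairs the target of one section with a rate derived from the other, a combination that the article never makes.
- **That the allowance might be 60%**, from reading 24 as a total of 12 per group. The missing label permits the reading, but the move to 30 in each group and the per-group wording in Anticipated results point the other way.
- **That finishing with 24 per group would fail the plan.** The evaluable number is a planning figure, and the protocol sets no such test.
- **That losses are predicted to exceed the margin.** The remark in Anticipated results about higher drop-out over a long trial directly introduces the five extra participants, and reads as the reason for them.

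**Conclusion.** The contradiction is real. The calculated sample size is given as 24, unlabelled, in the Sample size section and as 25 per group in Anticipated results, for the same calculation. If 24 is per group, the implied spare is 6 or 5 participants per group. The practical effect is small, with enrolment unaffected and power differing by at most about 2 percentage points across the assumptions tabulated.

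The mismatch itself rests on no assumption beyond reading the two sentences. The derived percentages assume that 24 is per group. The power figures assume an independent two-group comparison of the printed means. Under that comparison, two-sided with the pooled SD, neither 24 nor 25 per group reproduces 80%. Choosing one of the two numbers would therefore make the text consistent without making the power statement correct.

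**What to change.** State one evaluable number, labelled per group, in both the Sample size and Anticipated results sections. Next to it give:

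- the drop-out rate actually assumed from the cited adherence reports;
- the test, its sidedness and the SD used;
- the power which that number gives for the printed means and SDs.

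Leave enrolment at 30 per group. Do not choose a rate merely because it turns 24 or 25 into 30. If the assumed rate and the evaluable number do not lead exactly to 30, say so and report the figures as they are.

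Reconciling the two sections costs a sentence or two. Restating the power means returning to the calculation on file or rerunning it, with no change to enrolment or trial conduct.

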## Abbreviations

CREB: cAMP response element-binding protein
CRF: case report from
DTC: dual task cost
EDTA: ethylenediaminetetraacetic acid
EEG: electroencephalography
EF: executive function
FA: fatty acid
FES-I: falls efficacy scale international
FITT: frequency, intensity, type and time
GDS: geriatric depression scale
ID: identification
LCPUFA: long chain polyunsaturated fatty acid
MEP: motor evoked potential
MMSE: mini mental state examination
NS: nutritional supplementation
PE: physical exercise
PFC: prefrontal cortex
RC: recruitment curve
RMT: resting motor threshold
RRP: response-related potential
TAP: test for attentional performance
TMS: transcranial magnetic stimulation
VG: video game.
